#### Ethics and informed consent

The research protocol was primarily submitted to both the local Medical Ethics Committee (MEC) of the AMC and the VUmc to be reviewed. Both committees have been accredited to judge studies for the Central Committee on Research Involving Human Subjects and determined that the proposed study is not subject to the Medical Research Involving Human Subjects Act (WMO) and that therefore no further judgment is required for the study. Informed consents are not required from patients.

### Data analysis

The main analyses of primary and secondary outcomes will be conducted for all randomized patients according to the result of the randomization (intention-to-treat). Additional analyses include:

(1) Per-protocol analysis excluding patients that are transported to a different hospital rather than the result of the assignment procedure.

(2) Analysis of included patients treated either in the AMC or the VUmc independent of the randomization through the assignment procedure.

We will conduct both unadjusted and adjusted analyses. We will use gender, mechanism of trauma (sharp/blunt), initial Glasgow Coma Scale (GCS), RTS score and the presence of intubation to adjust for possible differences in severity of trauma between the AMC and VUmc patients.

For subgroup analysis the following analyses will be performed:

Hemodynamically unstable patients (non-responders (SBP < 90) vs. transient responders (SBP > 90 with continuous fluid requirement)); Sharp vs. blunt trauma patients; Patients prehospitally treated by Mobile Medical Teams; Neurotrauma patients; Presence or absence of a seatbelt sign; Torso trauma vs. isolated extremity trauma; Intubated vs. spontaneously breathing.

For final analysis standard statistical techniques will be used to compare the different outcomes between the two hospitals.

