### Endpoints

The primary outcome criterion used is the number of days spent outside the hospital in the first year following the trauma. This outcome is responsive to differences in mortality (no additional days outside hospital), to differences in hospital stay for the initial admission and to differences in readmission rate.

The secondary outcome parameters include general health outcome at 6 and 12 months after the shockroom admission (using the EuroQol and HUI-3 questionnaires), morbidity and mortality during the first year following the trauma and various time intervals and process of care parameters of the initial admission (time to intervention, time to active bleed management, ICU and total hospital stay, etc.). Furthermore the radiation dosage is calculated in both strategies based on the actual number and type of radiological examinations related to the initial trauma performed in each patient during the first year.

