### Randomization

Randomization will be performed at the "Meldkamer Ambulancezorg Amsterdam" (MKA), the organization in charge of the coordination and distribution of ambulances and patients. Randomization will be performed using a computer program on a 1:1 basis with varying block sizes of 8, 12, and 16. Ambulance personnel will receive instructions according to the outcome of the randomization. Each eligible patient involved in a specific accident will be randomized. After each randomization, there is a pre-specified time interval of 1 hour in which eligible patients will be automatically transported to the other trauma center in order to minimize peak pressure in the study centers and guarantee optimal utilization of the two trauma centers. These patients are included in the trial, but are not formally randomized. In extreme cases, prehospital ambulance personnel can decide to waive the outcome of randomization, if they deem that the status of the patient requires the immediate attention of the closest hospital and death is imminent.

Because the distance between the two hospitals is relatively short (8 km) no significant delay in treatment by patient transport is encountered regardless of the outcome of the randomization.

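### The per-protocol and treated-hospital analyses are open to severity bias, because the only override of allocation described is for imminent death; a complier-average estimate should carry any claim about receiving shockroom CT

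*Protocol article*

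**What the plan says.** The main analyses in the Data analysis section of the Protocol article are run "for all randomized patients according to the result of the randomization (intention-to-treat"). Two further analyses follow:

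- Analysis (1) removes those who did not reach the assigned hospital: "Per-protocol analysis excluding patients that are transported to a different hospital rather than the result of the assignment procedure".
- Analysis (2) instead groups everyone by where they were treated: "Analysis of included patients treated either in the AMC or the VUmc independent of the randomization through the assignment procedure".

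Unadjusted and adjusted versions are planned. The adjustment set is gender, injury mechanism, initial GCS, RTS and intubation, used "to adjust for possible differences in severity of trauma between the AMC and VUmc patients".

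The Randomization section describes one way in which a randomized patient may leave the allocated hospital: "In extreme cases, prehospital ambulance personnel can decide to waive the outcome of randomization". The condition is that the crew judges that the patient "requires the immediate attention of the closest hospital and death is imminent".

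A separate rule there sends eligible patients arriving in the hour after a randomization to the other center. Of them the section says: "These patients are included in the trial, but are not formally randomized".

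On the primary outcome, days outside hospital in the first year, the Endpoints section states: "This outcome is responsive to differences in mortality (no additional days outside hospital").

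**The concern.** Departure from allocation is tied by rule to the strongest prognostic state in the trial, and death stops the outcome from accruing. Analyses (1) and (2) then exclude or regroup patients on that same event.

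- **Per-protocol.** A near-fatal patient allocated to the closer hospital stays in the set. A similar patient allocated to the farther hospital is taken to the closer one and drops out.
- **Treated-hospital.** All such patients are counted at the closer hospital, whatever their allocation.

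If these patients are more often nearer to one center, that center carries more deaths for reasons unrelated to CT location. The adjustment set captures much of what marks severity. However, the waiver rests on crew judgement, so residual confounding cannot be ruled out, and unadjusted versions are planned as well. At stake is whether a difference in (1) or (2), or a disagreement with intention-to-treat, would be taken as the effect of actually receiving shockroom CT.

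**Working it through.** **The plan's own figure.** Inputs from Sample size: difference 2 days, SD 12 days, two-sided 0.05, power 0.80. The formula gives n = 2 × [12 × (1.960 + 0.842) / 2]² = 565.1, so 566 per group. The stated 562 is 0.7% lower, with power 0.798. It reproduces, and the 2-day target is the yardstick below.

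**Assumptions (none is in the article).** w = share of patients who would be waived to the closest hospital, 1-3%. q = share of these closer to one given hospital, 0.5-0.7. Mortality is 60% in waivable patients and 5% in others. Each death costs 350 days. There is no true effect of hospital and no covariate adjustment.

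**Per-protocol.** Mortality in the hospital with share q is [w·q·0.60 + (1−w)·0.05] / [w·q + 1−w]. The other hospital has 1−q in place of q. Bias is the difference × 350.

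For w = 0.02, q = 0.7: 5.775% against 5.335%, a bias of 1.54 days.

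**Treated-hospital.** The same expression with 2wq in place of wq, because waivable patients from both arms go to the closer hospital.

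For w = 0.02, q = 0.7: 6.528% against 5.665%, a bias of 3.02 days.

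| w | q | per-protocol bias (days) | treated-hospital bias (days) |
|---|---|---|---|
| 1-3% | 0.5 | 0 | 0 |
| 2% | 0.6 | 0.77 | 1.51 |
| 2% | 0.7 | 1.54 | 3.02 |
| 3% | 0.7 | 2.31 | 4.48 |

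The bias counts against the hospital that is closer to more of the waivable patients.

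**Against sampling error in the same model.** At w = 0.02, overall mortality is 0.02 × 0.60 + 0.98 × 0.05 = 6.1%. The SD from mortality alone is 350 × √(0.061 × 0.939) = 83.8 days, and the standard error with 562 per arm is 83.8 × √(2/562) = 5.0 days. At q = 0.7 the biases are 1.54/5.0 = 0.31 and 3.02/5.0 = 0.60 standard errors, which would raise a 5% two-sided error rate to about 6% and 9%. At w = 0.03, q = 0.7, the standard error is 5.2 days, the ratios are 0.44 and 0.86, and the error rates are about 7% and 14%.

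**Check by simulation.** Four million patients, true effect 2 days, 2% waivable, 60% of them nearer the AMC, a 200-day deficit in waivable patients. About 1% of all patients cross over. Results in days: intention-to-treat 2.00 (expected 2 × 0.98 = 1.96), per-protocol 1.22, treated-hospital 0.42, complier-average 2.04.

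**Cost in precision.** The complier-average estimate is the intention-to-treat estimate divided by (1−w). With w of 1-3%, an intention-to-treat effect of 2.00 days becomes 2.02 to 2.06, and the interval widens by the same factor. Power at 562 per group for a 2-day complier effect is 0.790 at w = 1% and 0.782 at w = 2%, using the plan's SD of 12.

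**The case against.** Much of the case on the other side stands.

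- **Balance removes the bias.** A reader might infer from the waiver rule that both analyses *are* biased. The article does not support that. Waived patients go to the closest hospital, so net bias needs an uneven split by closest hospital, and no split or waiver rate is given. At q = 0.5 the bias in this model is zero.
- **The size rests on assumptions.** The assumed mortality implies an SD of about 84 days, far above the planned 12. Setting the bias against the 2-day target alone makes it look more decisive than it would be in data with that spread.
- **The plan already mitigates.** Intention-to-treat is the main analysis, (1) and (2) are additional, and GCS, RTS and intubation are in the adjusted model. The figures above are unadjusted and so may overstate what would remain.
- **A complier-average effect answers a different question.** A reader might infer that it could replace both analyses. It describes patients who would follow allocation, so it leaves out those waived for imminent death. Analysis (2) covers included patients, the word the Randomization section uses for the one-hour-rule patients who were not formally randomized. It therefore appears to be the analysis that brings them in, and deleting it is not justified.
- **The gain over intention-to-treat is small.** With few waivers the complier-average estimate is intention-to-treat slightly rescaled.

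These points limit the size and the remedy. They do not remove the exposure: both analyses still select or group on an event that the plan ties to imminent death. Being close to intention-to-treat is also what makes the complier-average estimate a safe basis for a statement about receiving shockroom CT.

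**Conclusion.** The point holds as a vulnerability. Analyses (1) and (2) are open to confounding by severity if waived patients are unevenly split by closest hospital, and covariate adjustment cannot be assumed to remove it. The possible size, unadjusted, is 0 to 2.3 days for per-protocol and 0 to 4.5 days for treated-hospital. This assumes 1-3% waivable, 50-70% closer to one hospital, mortality of 60% against 5%, and 350 days lost per death. The upper ends exceed the 2-day target but stay below one standard error in the same model. The main analysis is unaffected. The article does not show that either analysis is in fact biased, or in which direction.

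**What to change.** - Keep intention-to-treat as the main analysis.
- In formally randomized patients, add a complier-average estimate with randomized allocation as the instrument for hospital reached (two-stage least squares, or the ratio estimator with a bootstrap interval). Use it in place of the per-protocol result for any statement about the effect of actually receiving shockroom CT.
- State that it applies to patients who would follow allocation. State also that it needs the exclusion restriction (allocation acts on outcome only through the hospital reached) and monotonicity (nobody goes to a hospital only because the other was allocated). Both are plausible here but not guaranteed.
- Keep analyses (1) and (2), labelled descriptive and non-causal, and say in (2) how the one-hour-rule patients enter.
- Report the number of waived patients by randomized arm and hospital reached.

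The cost is a slightly wider confidence interval (about 1-3% at the waiver rates assumed here) and a little more analysis work. Allocated and treating hospital are already needed for the planned analyses.

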### Study group

All acute trauma patients are eligible for inclusion for the REACT trial when transported by the ambulance or helicopter to the AMC or VUmc shockroom according to the current pre-hospital triage system based on: Injury mechanism, Revised Trauma Score (RTS) and presence of traumatic brain injury. These factors determine the level of care that has to be present in the facility to which patients are transported.

The exclusion criteria for subsequent follow-up and analysis are patients younger than 16 years of age and patients who die during transport to the hospital.

The start of the study was scheduled for 1-11-2005.

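### The stated covariate list for the adjusted analysis leaves out age, which costs precision in the randomised comparison and leaves a possible confounder in the non-randomised ones

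*Protocol article*

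**What the plan says.** All references are to the protocol article.

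- **Data analysis, covariates.** "We will use gender, mechanism of trauma (sharp/blunt), initial Glasgow Coma Scale (GCS), RTS score and the presence of intubation to adjust". The stated purpose is to "adjust for possible differences in severity of trauma between the AMC and VUmc patients". The list is given outright, not as examples, and age is not in it.
- **Data analysis, populations.** "The main analyses of primary and secondary outcomes will be conducted for all randomized patients according to the result of the randomization (intention-to-treat". Two further analyses follow: a per-protocol analysis, which drops patients taken to a hospital other than the assigned one, and an analysis by the hospital that actually treated the patient. On modelling, the section says "We will conduct both unadjusted and adjusted analyses".
- **Study group.** "The exclusion criteria for subsequent follow-up and analysis are patients younger than 16 years of age". No upper age limit is given. The Sample size section repeats age under 16 as a reason for exclusion.
- **Endpoints.** "The primary outcome criterion used is the number of days spent outside the hospital in the first year following the trauma". The section explains that this measure responds to mortality, the length of the initial stay and readmission.
- **Randomization.** Allocation is 1:1 in varying blocks, with no stratification by age described. Eligible patients arising within 1 hour of a randomisation go to the other centre and are included without formal randomisation. Ambulance crews may set the allocation aside in extreme cases.

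**The concern.** A trial of everyone aged 16 and over covers a wide age range. Age plausibly bears on both death and time in hospital, and so on days outside the hospital. It is fixed before allocation, so the assigned hospital cannot affect it, even if it is written down only after arrival. It must also be known before anyone enters follow-up and analysis. An adjusted analysis that includes gender but not age therefore passes over a useful covariate that is already at hand.

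Two things are at stake. In the intention-to-treat comparison it is precision. In the comparisons that randomisation does not protect, it is confounding: if the patients diverted from their assigned hospital, or those sent by the 1-hour rule, differ in age between the two hospitals, the planned adjustment cannot correct for it.

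**Working it through.** **Inputs from the Sample size section:** difference 2 days, common SD 12 days, two-sided 5% level, power 0.80, 562 per group.

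**Assumed input:** R², the share of outcome variance that age explains. The documents give no value, so 1%, 5% and 10% are shown.

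**Step 1. Reproduce the plan's figure.**
n per group = 2 × SD² × (1.960 + 0.8416)² / difference² = 2 × 144 × 7.849 / 4 = 565.1, rounded up to 566. The stated 562 is 0.7% lower, so the figure reproduces as a comparison of two means without covariates.

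**Step 2. Power at the stated size without age.**
SE = 12 × √(2/562) = 0.716 days. Power = Φ(2/0.716 − 1.960) = Φ(0.834) = 79.8%.

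**Step 3. Power with age in a linear model.**
Residual SD = 12 × √(1 − R²); then as in steps 1 and 2.

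| Assumed R² of age | Residual SD (days) | Power at 562 per group | n per group for 80% power |
|---|---|---|---|
| none | 12.00 | 79.8% | 566 |
| 1% | 11.94 | 80.2% | 560 |
| 5% | 11.70 | 81.8% | 537 |
| 10% | 11.38 | 83.8% | 509 |

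The protocol gives no residual SD after its five covariates, so the calculation starts from 12. Set against the planned adjusted model, R² should be read as the share of the variance those five leave over that age explains.

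**Step 4. Where randomisation does and does not protect.**

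- *Intention-to-treat, randomised patients.* Age is balanced in expectation. Leaving it out does not bias the difference in means; step 3 is the whole cost.
- *Per-protocol.* Patients are removed because of what happened after allocation. The waiver applies to the most severely affected, so the remaining groups need not be balanced on age.
- *By treating hospital.* The comparison ignores the allocation, so balance on age is not assured.
- *Patients of the 1-hour window.* Their hospital follows from the preceding randomisation and is not drawn for them, so they too lack the formal guarantee.

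The documents contain no age data, so the size of any confounding cannot be calculated. What can be said is that the adjustment set contains no term for it.

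**The case against.** **The aim is severity.** The adjustment is declared to be for differences in severity of trauma, and most of the list fits that aim. On that reading age was left out on purpose. This explains part of the choice, but gender is no measure of injury severity and is on the list, so the stated aim does not account for the absence of age.

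**The gain is small and assumed.** This stands. At R² of 1% the gain is 0.4 percentage points of power, at 10% it is 4. The choice of covariates is partly a matter of judgement.

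**Age is not shown to be recorded.** No data collection list is printed. That age is available is an inference, though a firm one, since the exclusion cannot be applied without it.

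A reader might also infer three stronger points, which the documents do not support.

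- *That chance imbalance in age could mislead the main comparison.* The standard error of the unadjusted test already allows for it. The SD of the shift that chance imbalance produces is 12 × √R² × √(2/562), or 0.07, 0.16 and 0.23 days at R² of 1%, 5% and 10%. That is small beside the standard error of 0.716 days, which already contains it.
- *That two primary tests are planned, so the type I error is inflated.* The text promises both unadjusted and adjusted analyses but calls neither primary, and nowhere says that success on either would suffice. Naming the deciding model is commonly left to a full protocol or analysis plan, which is not shown here.
- *That intubation may be recorded after arrival and so be affected by the allocation.* The article does not state when it is recorded, and such a definition may well stand in the full document.

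**Conclusion.** The point holds as a modest and inexpensive improvement. The article fixes an adjustment set without age, although the trial must ascertain age and it plausibly predicts the main components of the primary outcome. For randomised patients the price is precision alone: power of 79.8%, against about 80.2% to 83.8% if age explains 1% to 10% of the variance. For the per-protocol and as-treated analyses, and for the patients who are not formally randomised, age could also confound, by an amount the documents do not allow one to estimate.

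This rests on three assumptions: that age predicts death and stay in this population, that R² lies in the range shown, and that a linear model with the protocol's SD of 12 days is adequate. The omission does not make the main comparison invalid, and it does not call the sample size into question.

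**What to change.** In the Data analysis section, add age as a continuous covariate to the list of gender, mechanism, GCS, RTS and intubation. Use the same list for the adjusted versions of the intention-to-treat, per-protocol and as-treated analyses.

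The cost is one phrase. No new data should be needed, since age must already be established for eligibility, and the sample size stays at 562 per group. The change should be made before outcomes are compared by hospital, so that it cannot depend on the results.

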## Discussion

The REACT trial is a multicentered, prospective randomized trial that evaluates the effect of the newly introduced Amsterdam Trauma Workflow concept on trauma care. The main goal of the Amsterdam Trauma Workflow concept is to minimize the total diagnostic work-up time of the initial trauma evaluation by integrating all diagnostic modalities in the trauma resuscitating room. This concept makes it possible to perform CT imaging earlier during the trauma evaluation without the need to transport the patient to the radiology department. This adjustment will likely result in a faster and improved workflow of trauma patients, that leads to a more complete diagnostic workup in the early phases of trauma resuscitation. This could potentially change therapeutic management options and eventually lead to a better outcome in severely injured trauma patients. The direct availability of CT scanning during the entire trauma resuscitation phase could mean that this could become available for even hemodynamically unstable patients

A second advantage of this concept is the reduction in the number of patient manipulations, patient transfers and transports. Generally, these actions can have the aforementioned, adverse effects, which could expose the already critically ill patients to extra dangers. However, the introduction of the multifunctional radiolucent patient treatment table, that is suitable for resuscitation, conventional diagnostic imaging and CT scanning, minimize these actions and their additional risks.

While the REACT study design enables us to describe the diagnostic and therapeutic procedures following initial CT scanning on an individual patient level, the REACT trial also gives us the opportunity to evaluate its effect on an institutional level.

Because of the additional CT scanning capacity that was created by adding the sliding CT scanner that services the two mirrored trauma rooms, logistics for the radiology department will be influenced for both acute (trauma) patients and elective CT scanning. By potentially eliminating the need to reckon with unplanned acute CT imaging, the regular elective CT scans can be planned better and more efficient, possibly leading to a reduction of waiting times and waiting lists. Critically ill patient groups (i.e. trauma patients and patients with intracranial bleedings, acute aneurysms or abdomens, ICU patients, etc.) who need CT scanning can have their total diagnostic work-up completed in the shockroom before transport to their destination of treatment. In some cases the diagnostic work-up can even be completed simultaneously for two patients because of the mirrored shockroom design.

Furthermore, the REACT study design enables us to describe in detail the diagnostic and therapeutic procedures following initial CT scanning of trauma patients in the shockroom or at the Radiology Department. We may be able to demonstrate a trade-off in the volume and cost of health care use between early detection of injuries and timely therapeutic management on one hand and late detection by additional diagnostic testing and subsequent therapies on the other.

Another possible institutional effect might be that a shockroom CT scan may be used as an attractive alternative to other imaging procedures or to sequential diagnostic testing strategies in other patient groups (for instance stroke patients, patients with acute abdominal pain, etc), since it remains an all-inclusive multifocal diagnostic modality. As a consequence substitution of diagnostic modalities or changes in patient groups presenting for CT scanning may occur as a result of joint production.

Finally, the total costs of realizing this concept are of substantial amount and therefore this shockroom design has to be assessed during the study period in a cost-effectiveness analysis.

